### Sample size {14}

As this study is an exploratory clinical trial with the application of cutting-edge technology, a small sample randomized controlled method was designed to be carried out. Based on the literature review and our team’s preclinical experimental results, the sample size met the minimum requirements combined with the budget and actual situation of the project. The osteotomy accuracy in the previous study was 1.99 ± 1.32 mm and power *α* is set as 0.05 and (1 − *β*) as 0.9. Therefore, *n*1 = *n*2 = $${\left[\frac{{Z}_{\frac{\alpha }{2}}+{Z}_{\beta }}{\delta /\sigma }\right]}^{2}({Q}_{1}^{-1}+{Q}_{2}^{-1})$$×½≈9.24 [13]. Considering the loss of follow-up (10%), the experimental and control groups will enroll 11 cases in each group.

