## Trial design {8}

This trial is a prospective randomized controlled trial. There are two parallel groups, including the experimental group of patients receiving the EM navigation system based on the artificial intelligence for osteotomy and the control group having the MDO surgery in a traditional method that surgeons perform the osteotomy on their own experience. The allocation ratio of the two groups is 1:1. The framework of this trial is shown in Fig. 1.

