### Outcomes {12}

#### Primary outcome

The primary outcome will be the accuracy of osteotomy by comparing the preoperative design and postoperative CT. The two mental foremen and the condylion of the unaffected side are marked as the registration points. Altogether, 10 points on the osteotomy plane of each pre- and postoperative CT scan are selected to calculate the accuracy (Fig. 4a). Each patient’s data will be measured three times to avoid measurement bias, and the staff responsible for measurement are blinded to the patient’s grouping information.

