## Statistical methods

### Statistical methods for primary and secondary outcomes {20a}

The SAS software (version 9.4, SAS Institute, USA) will be used to analyze and process primary and secondary outcomes.* N* (%) and mean ± standard deviation (SD) with median and interquartile range shall describe all quantitative data. If the data follows a normal distribution, we use Student’s* t*-test to compare the two groups. For comparing enumeration data across groups, a sample size of less than 40 necessitates using Fisher’s exact test. *P* < 0.05 is deemed statistically significant.

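### The stated 90% power is unsupported: no between-arm difference is given, and n ≈ 9.24 reproduces when one earlier series' mean error (1.99 mm) is entered as that difference

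*Protocol article*

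**What the plan says.** The protocol article, Sample size {14}, calls the trial exploratory and ties its size to the literature, the team's preclinical results and the budget. It then gives a formal calculation. The only data supplied are "The osteotomy accuracy in the previous study was 1.99 ± 1.32 mm". Alpha "is set as 0.05 and" power (1 − β) "as 0.9. Therefore" lead into a two-group formula in δ/σ, with result 9.24 per group. The section ends: "Considering the loss of follow-up (10%), the experimental and control groups will enroll 11 cases in each group".

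The section does not give a value for δ, an expected mean for either arm, or the technique, arm or population of the previous study.

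Primary outcome defines what accuracy means here: "The primary outcome will be the accuracy of osteotomy by comparing the preoperative design and postoperative CT". Trial design {8} adds: "The allocation ratio of the two groups is 1:1". Statistical methods {20a} plans Student's t-test between the two groups if the data are normally distributed, with significance at P < 0.05.

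**The concern.** The formula needs a difference between two arms. Accuracy, as the protocol defines it, is a deviation from plan within each patient, so a mean of 1.99 mm describes how far one series missed its plan. It says nothing about how far two techniques differ. If that mean was used as δ, the power statement assumes an effect as large as the whole error of the earlier series, and no comparator value shows that such an effect is expected.

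The consequence concerns interpretation. The Discussion says the data will be used to refine the design of a later trial. A non-significant result taken to come from a 90%-powered study could wrongly count against navigation, and the same choice of δ could be carried into the next sample size.

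**Working it through.** **Inputs.** Mean 1.99 mm, SD 1.32 mm, α = 0.05 two-sided (the formula uses Z at α/2), power 0.90 and 10% loss, all from Sample size {14}. 1:1 allocation from Trial design {8}, so Q₁ = Q₂ = 0.5. Two-sample t-test from Statistical methods {20a}.

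**1. Reproducing the plan's figure.** The formula is n = [(Z_{α/2} + Z_β)/(δ/σ)]² × (1/Q₁ + 1/Q₂) × ½. Enter δ = 1.99 and σ = 1.32:

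- δ/σ = 1.99/1.32 = 1.508
- n = [(1.96 + 1.28)/1.508]² × (2 + 2) × ½ = 9.238, the printed 9.24 (9.246 with unrounded normal quantiles)
- 9.24/0.9 = 10.3, rounded up to the planned 11

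With the same δ and σ, two variants miss: one-sided α gives 7.54, and 80% power gives 6.91. The formula fixes only the ratio δ/σ, so this does not prove which δ was used. But the only two figures printed give that ratio.

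**2. What δ = 1.99 mm implies for the arm means.**

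- If 1.99 mm is the control error: navigated mean = 1.99 − 1.99 = 0 mm. For an unsigned distance, a mean of zero is incompatible with any spread.
- If 1.99 mm is the navigated error: control mean = 1.99 + 1.99 = 3.98 mm.

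Neither pair of means appears in the document.

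**3. Power at the planned size.** Two-sided t-test at 0.05, noncentral t with df = 2n − 2 and noncentrality (δ/σ)√(n/2). The SD of 1.32 mm in both arms is an assumption.

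| True difference (mm) | 11 per arm | 10 per arm |
|---|---|---|
| 1.99 | 92% | 89% |
| 1.2 | 53% | 49% |
| 1.0 | 39% | 36% |
| 0.66 | 20% | 19% |
| 0.5 | 14% | 13% |

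Example, 1.0 mm with 11 per arm: noncentrality = (1.0/1.32) × √5.5 = 1.78, df = 20, power 39%.

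**4. Sensitivity to the SD.** For a halved error (δ = 1.99/2 = 0.995 mm) with 11 per arm:

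| Common SD (mm) | Power |
|---|---|
| 1.32 | 39% |
| 1.0 (assumed) | 60% |
| 0.8 (assumed) | 79% |

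If only the navigated arm's SD halves, to 0.66 mm, simulated power is about 53% with 10 per arm and 57% with 11.

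**5. What the design can detect, SD 1.32 mm in both arms.**

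| Completers per arm | 90% power | 80% power |
|---|---|---|
| 11 | 1.92 mm | 1.66 mm |
| 10 | 2.02 mm | 1.75 mm |

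Expected 95% CI half-width with 11 per arm: t(0.975, 20) × 1.32 × √(2/11) = 2.086 × 0.563 = 1.17 mm.

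**The case against.** **The exploratory label.** The trial calls itself exploratory, admits budget limits, and says in its Discussion that the sample is small and a larger multi-centre trial should follow. This makes it less likely that a null result is read as definitive, and it is a good reason to leave the sample alone. It does not support the 90% figure, which the article states without qualification.

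**δ is never named.** This stands: the use of 1.99 mm as δ is an inference from the reproduced result. If another δ was meant, the section omits its key input and needs the same correction.

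**A stronger reading.** A reader might infer that 90% power holds only if navigation removes the whole osteotomy error, or that it fails for any plausible gain. The documents do not support this. They do not say which technique or arm the 1.99 mm describes. If it came from a guided or navigated series, the free-hand error is unknown and could be larger. The Background describes the intraoral approach in young children as difficult.

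**The SD.** A reader might also take 39% as the trial's power for halving the error. It depends on 1.32 mm holding in both arms. The document does not say whether 1.32 mm is a between-patient SD. The primary outcome uses 10 points per plane and three measurements per patient, so a patient-level average could vary less. The SD might also fall along with a smaller mean. The range in step 4 is therefore part of the result.

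**Conclusion.** Wrong as written. The arithmetic is sound; the fault lies in the assumption put into it. The section gives no between-arm difference, and its result reproduces when a one-series mean error takes that place, so the 90% power is unsupported.

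The size depends on two things the document leaves open: the true difference and the between-patient SD. At 11 per arm, power ranges from 92% (1.99 mm, SD 1.32 mm) to about 39% (1.0 mm, same SD). For a halved error the span is 39% to 79% as the SD goes from 1.32 to 0.8 mm, so over this whole range it stays below 90%. Whether a difference near 1.9 mm is realistic cannot be settled from the document.

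**What to change.** Keep 22 patients. In Sample size {14}, withdraw the unqualified 90% claim, name δ as a between-arm difference, and give its source. Say also which technique and population the 1.99 ± 1.32 mm describes. Then state:

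> Assuming a between-patient SD of 1.32 mm in both arms, 11 per arm gives 90% (80%) power for a mean difference of 1.92 mm (1.66 mm) and about 40% for 1.0 mm; with 10 completers per arm the detectable differences are 2.02 mm (1.75 mm); the expected 95% CI half-width with 11 per arm is about ±1.2 mm.

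If the previous study's SD is not a between-patient SD, replace it and recompute these figures. The cost is a rewording of one section and a less favourable power statement; no patients, visits or design features change.

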### Recruitment {15}

The participants will be recruited at the Ninth People’s Hospital School of Medicine, Shanghai Jiao Tong University, one of the top plastic and reconstructive surgery centers nationally (the statement came from the 2022 China Hospital Specialty Comprehensive Ranking, a public interest discipline assessment project conducted by the Institute of Hospital Management of Fudan University as an independent third party), with hundreds of craniofacial surgeries performed yearly. When visiting our craniofacial clinic, HFM patients who meet the inclusion criteria will be introduced to this trial. If the patients or their parents are interested in attending the trial, they will be contacted by our staff to receive detailed information about this trial and sign the consent when they are hospitalized.

## Assignment of interventions: allocation

### Sequence generation {16a}

The SAS software is adopted for block randomization. It generates a random table for grouping, and the ratio of the experiment and control groups is 1:1. The statistician who does not participate in the operation divides the enrolled patients into groups according to the sequence of random numbers. The grouping information is sealed in the envelope and saved by the researchers who did not participate in the operation. All the enrolled subjects are treated in the experimental or control group according to the numbers shown in the random envelope to avoid bias caused by the non-random selection of samples.

### Concealment mechanism {16b}

The statistician in the surgery generates the random table for grouping by the SAS software. The researcher who does not participate in the surgery saves the grouping information in sealed envelopes. The random distribution list is confidential; every patient has a specific ID number. A specific staff is responsible for telling the surgeon which kind of operation the enrolled patient should receive. The grouping information and the identifiable information are saved in sealed envelopes separately.

### Implementation {16c}

First, the trial team’s investigators will be responsible for recruiting people who meet the inclusion criteria and obtaining permission. The study statisticians then do the randomized allocation and send the patient’s randomized number. Depending on the allocation, the surgeons will execute the procedure for the patient with or without the robotic navigation system. Finally, the engineer who is unaware of the allocation measures the outcomes.

## Assignment of interventions: blinding

### Who will be blinded {17a}

The trial will be conducted single blindly. Knowing which way to intervene, the operator is unable to be blinded. The recruited patients and outcome assessors have no idea if they are receiving surgery with the navigation system.

### Procedure for unblinding if needed {17b}

Only the patients and outcome assessors are blind in this single-blind trial; under no circumstances do they need to be unblinded.

## Data collection and management

### Plans for assessment and collection of outcomes {18a}

The image data from the preoperative and postoperative procedures will be transferred into Geomagic Control X (3D System, SC). The accuracy of the osteotomy plane is assessed after the registration.

The accuracy of the osteotomy between the preoperative plan and the postoperative result will be the primary outcome measure. The postoperative CT will be performed within 7 days following surgery, which is the most critical outcome for determining the efficacy of robotic navigation technology. Improvements in the symmetries of the mandibles will be assessed by comparing the CT 6 months after MDO and the preoperative ones with Mimics.

It will be organized for surgeons to record important information after surgery during the follow-up period for security measures such as intraoperative blood loss, operation time, hospitalization, possible blood transfusion, and complication rates.

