#### Intervention description {11a}

After obtaining the consent form, all patients of each group receive the preoperative 3D CT scan, and the data will be stored in DICOM format and imported into the corresponding processing software (Mimics 21.0, Materialise, Belgium). The surgeons adopt the Mimics software to reconstruct the mandibular and design the osteotomy line to avoid the inferior alveolar nerve inside the mandibular as in the preoperative plan (Fig. 2).

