**Fig. 4 Fig4:**
[figure not shown]
Postoperative imaging analysis. **a** Accuracy analysis by comparing the CT data 1 week after MDO with the preoperative design. **b** Symmetry analysis by comparing the image after removing the distractor with the original CT

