#### Secondary outcomes

The secondary outcome includes the symmetry of the mandibular, pain scale, recording of surgical complications, and satisfactory score.

The symmetry of the mandibular is evaluated by three indicators: the angle of inclination, the mandibular ramus’s height, and the mandibular body’s length, which will be obtained from the CT 6 months after the surgery (Fig. 4b).

The angle of inclination: A horizontal plane (HP) is established by selecting bilateral suborbital points (Or) and the healthy superior external auditory canal points (Po). Establish the occlusal plane (OP) from the adjacent medial point of the maxillary central incisor to the medial buccal cusp of the bilateral first molar. Measure the angle between the occlusal plane and the horizontal plane, set as angle A. The smaller angle A indicates the smaller deviation angle of the mandible and maxilla, meaning the better symmetry of the lower face.

The height of mandibular ramus: The height of mandibular rami, that is, the distance between condylion (Co) and mandibular gonion (Go), is measured respectively. The distance of the affected side is set as *h*, and the distance of the healthy side is set as *H*. Comparing the values of the affected and the healthy sides. The smaller the difference, the better the bilateral symmetry.

The length of the mandibular body: The menton (me) is marked, and the length of the bilateral mandibular body, the distance from the bilateral gonion (Go) to the menton (Me), is measured respectively. The distance of the affected side is set as *l*, and the distance of the healthy side is set as *L*. Comparing the values of the affected and the healthy sides, the smaller the difference, the better the bilateral symmetry.

The pain scale: The evaluation time is 1 week, 1 month, and 6 months after surgery. The pain scale is an international visual analog scale, with a scale from 0 to 10 representing no pain to the most intense pain.

The postoperative complications during the trial will be recorded, including local infection, bone nonunion, scar hyperplasia, occlusal disorder, nerve injury, and tooth germ injury.

The satisfaction score was evaluated by a modified 5-point Likert table, with 1–5 indicating unsatisfactory to very satisfied. It will be recorded at the 1-week, 1-month, and 6-month follow-up.

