### Data management {19}

The image data will be imported into Geomagic Control X (3D System, SC) and Mimics (Materialise, Belgium). The accuracy of the osteotomy will be the primary outcome of the effectiveness of robotic technology. The precision of the osteotomy plane will be assessed by pre- and postoperative CT within 7 days following surgery. Mandibular symmetries will be assessed according to the CT 6 months after the surgery.

This team will provide for doctors to record essential information after surgery during the follow-up period for security indicators such as intraoperative blood loss, operation time, hospital time, any blood transfusion, and rates of complications.

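### Mandibular symmetry is defined both as change from the preoperative CT and as the 6-month value; fix one endpoint and adjust it for the preoperative measurement

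*Protocol article*

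**What the plan says.** The protocol article describes symmetry in five places.

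- Plans for assessment and collection of outcomes {18a}: "Improvements in the symmetries of the mandibles will be assessed by comparing the CT 6 months after MDO and the preoperative ones with Mimics".
- Fig. 4 legend, panel b: "Symmetry analysis by comparing the image after removing the distractor with the original CT".
- Secondary outcomes, on the three indicators (occlusal plane angle A, ramus height, body length): "which will be obtained from the CT 6 months after the surgery".
- Data management {19}: "Mandibular symmetries will be assessed according to the CT 6 months after the surgery".
- Table 1: the symmetry row is ticked at 6 months only, with no baseline tick.

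For ramus height the Secondary outcomes section adds: "Comparing the values of the affected and the healthy sides. The smaller the difference, the better the bilateral symmetry". Body length is treated the same way. Neither text says whether the difference is absolute.

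For the analysis, Statistical methods {20a} covers primary and secondary outcomes together: "If the data follows a normal distribution, we use Student’s* t*-test to compare the two groups". No covariate is named. Intervention description {11a} states that "all patients of each group receive the preoperative 3D CT scan", so a baseline scan exists for every participant.

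**The concern.** Change from the preoperative scan and the value at 6 months are different variables with different variances. The article commits to both and then names one t-test without saying which it is applied to. Either could be picked once the data are known, and with 11 patients per arm the two can give different answers.

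The stated test also leaves information unused. On the 6-month reading, the preoperative value plays no part. On the change reading it is subtracted with a fixed slope of 1, which adds noise when pre and post values are weakly related. Regression on the preoperative value estimates the slope instead. It also largely removes the conflict: with the preoperative value as covariate, the estimated arm effect is the same whether the outcome is the 6-month value or the change from baseline.

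The Discussion says the data will be used to refine the design of a later trial. A symmetry result that could mean either variable serves that purpose poorly.

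**Working it through.** **Inputs.** 22 patients, 11 per arm (Sample size {14}); 1:1 allocation (Trial design {8}); preoperative CT for all ({11a}); unadjusted t-test ({20a}). The correlation r between preoperative and 6-month values and both SDs are not in the documents. Here r is assumed over 0 to 0.9.

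**The plan's own figure.** Nothing is computed for symmetry. The 11 per arm comes from the primary outcome and reproduces: [(1.960 + 1.282)/(1.99/1.32)]² × (2 + 2) × ½ = 9.25 (stated 9.24), and 9.25/0.9 = 10.3, rounded up to 11.

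**Formulas**, each relative to the variance of the 6-month-only t-test, with N = 22:

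- Change score: 1 + k² − 2rk, where k is the preoperative SD over the 6-month SD. With k = 1 this is 2(1 − r).
- ANCOVA: (1 − r²) × (N − 3)/(N − 4) = (1 − r²) × 19/18. The factor 19/18 is the average price of chance imbalance in a normal covariate. Error degrees of freedom fall from 20 to 19.

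The last column is the minimum detectable difference (MDD) at 80% power, in SDs of the 6-month value, from the noncentral t.

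| r | Change / 6-month (k = 1) | ANCOVA / 6-month | ANCOVA / change (k = 1) | MDD: 6-month, change, ANCOVA |
|---|---|---|---|---|
| 0 | 2.00 | 1.056 | 0.528 | 1.26, 1.78, 1.29 |
| 0.3 | 1.40 | 0.961 | 0.686 | 1.26, 1.49, 1.23 |
| 0.5 | 1.00 | 0.792 | 0.792 | 1.26, 1.26, 1.12 |
| 0.7 | 0.60 | 0.538 | 0.897 | 1.26, 0.97, 0.92 |
| 0.9 | 0.20 | 0.201 | 1.003 | 1.26, 0.56, 0.56 |

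**Break-even against the 6-month t-test.** (1 − r²) × 19/18 = 1 gives r² = 1/19, so r = 0.23 (0.24 on confidence-interval width, which also counts the lost degree of freedom). With 10 per arm completing, r² = 1/17, so r = 0.24 (0.26 on interval width).

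**Worst case.** Since 1 + k² − 2rk = (1 − r²) + (k − r)², the change-score variance is never below 1 − r², whatever the SDs. On average, ANCOVA's variance therefore cannot exceed that of either alternative by more than 19/18, or 5.6%.

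**Validity.** In a simulation of 20,000 trials with 11 per arm and no arm effect, all three tests rejected in 4.8% to 5.3% of trials at the 5% level.

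**The case against.** The strongest reply is that the planned test is valid. Its standard error already allows for chance baseline imbalance, symmetry is a secondary outcome of a trial the article calls exploratory, and covariate adjustment is commonly left to an analysis plan that is not shown. All of that stands. The absence of ANCOVA is not in itself an error. What the article does state, and states inconsistently, is the endpoint; adjustment is offered as a cheap improvement.

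A reader might infer more than the documents support:

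- *That adjustment is free.* It is not. Below r of about 0.23 it loses slightly to a 6-month-only t-test, and r is unknown. It could be low, because surgery aims to correct the preoperative asymmetry.
- *That the preoperative CT is ignored.* Section {18a} and the Fig. 4 legend use it. Against a change score, the gain shrinks to about 10% at r = 0.7 and vanishes at r = 0.9.
- *That a change score is noisier whenever r is below 0.5.* This needs equal SDs; in general the threshold is r = k/2.
- *That an over-lengthened side would score better than equality.* This requires a signed difference. In a sentence about symmetry, the natural reading is magnitude, so only a clarification is needed.
- *That dividing by the healthy side gains precision across ages 3 to 18.* The documents give no lengths or SDs from which to show it, and it cannot apply to angle A.

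One practical caution also stands. Experimental-arm patients are scanned preoperatively wearing a splint with steel spheres, which may reveal the arm to a blinded reader. This affects any use of that scan, including the change score already described.

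**Conclusion.** The point holds as an unresolved conflict between two definitions of a secondary endpoint, together with a stated analysis that may be less efficient than one available from data already collected. It is not a claim of invalid inference, and neither the sample size nor the primary outcome is affected.

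The choice between the two stated definitions matters by itself: with equal SDs, the change score has from 2.0 times (r = 0) down to 0.2 times (r = 0.9) the variance of the 6-month value. Adjustment avoids having to guess r. Its average loss is at most 5.6% in variance. Its gain over the 6-month t-test is about 4%, 21% and 46% at r = 0.3, 0.5 and 0.7; over the change score it is about 31%, 21% and 10%. These figures rest on an assumed r, a normally distributed covariate and, for the change-score comparison, equal SDs. The conflict between the sections rests on no assumption.

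**What to change.** 1. Reconcile {18a}, the Fig. 4 legend, Secondary outcomes, {19} and Table 1 on one endpoint: the 6-month value of angle A, and the absolute side-to-side differences in ramus height and body length.
2. In {20a}, specify for each indicator an ANCOVA of the 6-month value on arm, with the same preoperative measurement as covariate.
3. Add the preoperative symmetry measurement to the baseline column of Table 1, taken by the same method as at 6 months. Keep the splint from disclosing the arm, for example by having someone other than the 6-month assessor read the preoperative scan.
4. Scaling the side differences to the healthy side is optional. If wanted, state it in advance and justify it by interpretability.

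The cost is revised wording, one error degree of freedom per analysis, and five quantities per patient (angle A, two ramus heights, two body lengths) measured on a CT already taken. Treatment, visits and sample size do not change.
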